**Methods:**

The proposed project will be conducted in three phases. The first phase of the study will focus on cultural adaptation of the interventions through qualitative interviews with key stakeholders. The second phase will be to refine and produce manually assisted interventions. Third and last stage would be to assess the feasibility of the culturally adapted interventions through a factorial RCT. The study will be carried out in Karachi, Hyderabad, Peshawar, Lahore and Rawalpindi, Pakistan. Recruitment of participants will take place from primary care and volunteer organisations/drug rehabilitation centres. A total of 260 individuals diagnosed with SUD (*n* = 65) in each of the four arms will be recruited. The intervention will be delivered weekly over a period of 12 weeks in both individual and group settings. Assessments will be carried out at baseline, at 12th week (after completion of intervention) and 24th week post-randomisation. The analysis will determine the feasibility of recruitment, randomisation, retention and intervention delivery. Acceptability of intervention will be determined in terms of adherence to intervention, i.e. the mean number of sessions attended, number of home assignments completed, attrition rates, as well as through process evaluation to understand the implementation process, context, participants’ satisfaction, and impact of the study intervention. The health resource use and impact on the quality of life will be established through health economic data.

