## Methods

### Study design and setting

This will be a four-arm feasibility factorial RCT. An overview of complete study design is provided in Fig. 1. The proposed project will consist of three phases. The first phase of the study will focus on the adaptation/development of the intervention in accordance with the Pakistani culture. The second phase will include refinement of the interventions and production of the intervention manuals. The third phase will be to assess the feasibility through a factorial RCT. The study will be carried out in Karachi, Hyderabad, Peshawar, Lahore and Rawalpindi, Pakistan. Recruitment of participants will be from primary care and volunteer organisations/drug rehabilitation centres.

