### Phase 2: test run and intervention refinement

Phase 2 will involve preliminary testing of the culturally adapted intervention in a small group of participants. Cultural adaptation of the intervention requires an understanding of the religious and socio-cultural constructs of the population. This will take into consideration the explanatory models of any illness, along with understanding of underlying beliefs and values [31]. Such adaptations are reported to increase the acceptability and uptake of psychological and social interventions. Once the cultural adaptation is complete, a sample of 12 participants diagnosed with SUD will be invited to participate in the test run of the intervention. This will consist of 8 individual and 4 group sessions focusing on distinct yet related stages: exploring motivation to change; exploring the process of change; identifying strategies to consolidate commitment to change, explore effective coping skills, increase awareness and development of flexible responding in the presence of triggers of relapse. Feedback will be gathered from the participants, therapists and staff, on the relevance and acceptability of the culturally adapted interventions. All participants of trial run will be invited to be interviewed to explore their opinions on intervention relevance and acceptability. All interviews will be carried out by researchers from outside the local community in order to further protect interviewee confidentiality. These interviews will be recorded and transcribed. The interview guide will include some predetermined questions (based on findings from phase 1) and some open-ended questions to facilitate emergence of new themes.

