### Phase 3: feasibility factorial RCT

The feasibility of the intervention will be assessed using a factorial RCT, for MICBT and MBRP intervention, comparing four groups: (1) MICBT plus treatment as usual group (TAU), (2) MBRP plus TAU group, (3) the integrated MICBT and MBRP with TAU and (4) TAU group alone. In Pakistani culture, people consider themselves more as part of a family and larger community rather than as individuals. Therefore, a group approach is more culturally appropriate but for certain private/family issues the flexibility of some individual time with the therapists will be offered. The group sessions will consist of approximately eight participants.

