### Intervention allocation

#### Sequence generation

Participants will be randomly allocated to one of the four intervention arms by an independent offsite statistician using a computer-generated random sequence based on a block randomised design [46] until all study data are collected and verified. Once randomised, participants will be allocated a unique study identification number and informed about their intervention allocated groups within 1 week of randomisation.

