### Data analysis

#### Statistical analysis

The study data will be analysed using SPSS (Version-22). Analysis of data will take place after full recruitment and data collection. Descriptive data analysis will be performed to summarise demographic data and feasibility outcomes. Baseline and outcome assessment data will be summarised using the appropriate descriptive statistics and graphical summaries. As this is a feasibility study, the analysis of the data will be largely descriptive and will focus on confidence intervals for the difference amongst groups for each outcome measure. Possible between-group differences will be assessed using analysis of variance (ANOVA) and chi-square tests. The results of the trial will follow the standard CONSORT recommendations. A complete statistical analysis plan will be written prior to database lock and subsequently will be discussed and approved by the Trial Steering Committee (TSC). There is no interim analysis planned.

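### Three arms include group therapy and TAU alone does not, but the named ANOVA and chi-square tests treat participants as independent, so confidence intervals will be too narrow if outcomes correlate within therapy groups

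*Protocol article*

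**What the plan says.** All statements are in the protocol article.

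- **Arms and delivery.** Phase 3 compares MICBT, MBRP and their integration, each added to TAU, with TAU alone. It prefers a group approach on cultural grounds, with some individual time, and adds: "The group sessions will consist of approximately eight participants". The abstract's Methods paragraph describes mixed delivery: "The intervention will be delivered weekly over a period of 12 weeks in both individual and group settings". The CAMIAB intervention section also mentions both formats. The only session mix given is for the phase 2 test run: "This will consist of 8 individual and 4 group sessions".
- **Randomisation.** Under Sequence generation, individual participants are allocated by a "computer-generated random sequence based on a block randomised design".
- **Analysis.** Statistical analysis describes a mainly descriptive analysis centred on confidence intervals for differences between arms, and then states: "Possible between-group differences will be assessed using analysis of variance (ANOVA) and chi-square tests". A full analysis plan is promised before the database is locked.
- **Use of the results.** Sample size, and the section on missing data, say that the results will inform the sample size of a larger trial. The missing-data section adds inverse probability weights, which address missing follow-up and not dependence between participants.

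The article does not mention correlation within therapy groups, an ICC or a design effect.

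**The concern.** People who attend the same therapy group share sessions, group dynamics and peers, so their outcomes may be more alike than those of people in different groups. That can arise in three arms and not in the fourth. ANOVA and chi-square on individuals give each participant full weight as an independent observation. With positive correlation inside groups, the standard error of any contrast involving an active arm is then understated, and the interval is too short.

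Two things are at stake. First, the intervals that the plan puts at the centre of its between-arm analysis may claim more precision than the data hold. Second, the trial is meant to feed the sample size of a definitive trial. For a treatment delivered partly in groups, that calculation needs the therapy-group ICC as well as an effect size, and the named methods do not produce one.

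**Working it through.** The article gives no ICC or design effect, so it has no figure of its own on this point to reproduce. The check asks how far a naive interval would be wrong.

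**Inputs from the article**
- Group size m = 8 (Phase 3).
- n = 65 per arm (Sample size). 65 / 8 is about 8 groups per active arm.
- Attrition 30% (Sample size). Average observed group size is 8 × 0.70 = 5.6.

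**Assumption**
- ICC of 0.01, 0.05 or 0.10 in the active arms and none in TAU, with the same total variance in every arm.

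**Formulas**
- Design effect in an active arm: DE = 1 + (m − 1) × ICC.
- Ratio of true to naive standard error:
  - active versus active: √DE
  - active versus TAU: √((DE + 1)/2)
  - factorial margin, where three of the four cells are grouped: √((3DE + 1)/4)
- True coverage of a nominal 95% interval: 2Φ(1.96/ratio) − 1.

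**Worked case, m = 8, ICC = 0.05**
- DE = 1 + 7 × 0.05 = 1.35.
- Active versus active: √1.35 = 1.162, coverage 90.8%.
- Active versus TAU: √(2.35/2) = 1.084, coverage 92.9%.
- Factorial margin: √(5.05/4) = 1.124, coverage 91.9%.

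**Full groups of eight: SE ratio, then coverage**

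| ICC | DE | Active vs TAU | Active vs active | Factorial margin |
|---|---|---|---|---|
| 0.01 | 1.07 | 1.017, 94.6% | 1.034, 94.2% | 1.026, 94.4% |
| 0.05 | 1.35 | 1.084, 92.9% | 1.162, 90.8% | 1.124, 91.9% |
| 0.10 | 1.70 | 1.162, 90.8% | 1.304, 86.7% | 1.235, 88.8% |

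**After 30% attrition, m = 5.6**

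| ICC | DE | Active vs TAU | Active vs active |
|---|---|---|---|
| 0.01 | 1.046 | 94.7% | 94.5% |
| 0.05 | 1 + 4.6 × 0.05 = 1.23 | 93.7% | 92.3% |
| 0.10 | 1.46 | 92.3% | 89.5% |

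**Simulation under no treatment effect** (8,000 trials, 65 per arm, groups of eight in three arms). The ordinary four-arm ANOVA at a nominal 5% rejected in 4.9% of trials at ICC 0, 5.9% at 0.01, 10.0% at 0.05 and 16.2% at 0.10.

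**Check on city.** The article says: "The study will be carried out in Karachi, Hyderabad, Peshawar, Lahore and Rawalpindi, Pakistan". With individual randomisation and an assumed between-city ICC of 0.05 or 0.10, a two-arm test that ignores city rejected in 3.8% to 4.0% of trials when the arms were balanced by city, and in 5.1% to 5.2% when they were not stratified. Ignoring city leaves intervals slightly wide or about right.

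**The case against.** The strongest reply has four parts.

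- **The ICC is unknown and delivery is mixed.** Individual sessions outnumber group sessions in the test run, which may lower the ICC, and at 0.01 coverage is practically nominal. This stands. It makes the conclusion conditional, and a reader who infers that the intervals are certain to be too narrow goes beyond the documents. It does not make the independence assumption suitable, because Phase 3 itself favours a group approach.
- **Model detail belongs in the analysis plan.** This stands for the form of random effects, degrees of freedom and ICC reporting. Silence on the ICC does not show that it will not be estimated. The article does, however, name particular tests, and an analysis plan that follows them inherits the mismatch. Group membership also has to be captured while the groups run, whereas the analysis plan is due only before database lock.
- **The stakes are limited.** This stands. The progression criteria are percentages that do not rest on between-arm tests, there is no formal power calculation, and clustering of this kind affects precision and not the point estimates.
- **The five cities.** A reader might infer that running the trial in five cities also narrows the intervals, or that randomisation ought to be stratified by city. Neither is supported. Participants are randomised individually, the simulation shows no narrowing, and a condensed article that mentions blocks without listing strata does not show that strata are absent.

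A reader might also assume clustering by shared therapists. The article does not give therapist numbers or caseloads, so the point rests on the group sessions alone.

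**Conclusion.** The point holds in conditional form. The delivery format makes the design partially nested, and the between-arm tests named in the article ignore this. The resulting intervals are too short to the extent that outcomes correlate within therapy groups.

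The size depends on an assumed ICC. The loss of coverage is under one percentage point at 0.01. At 0.05 it is about 1 to 3 points after attrition and 2 to 4 points with full groups. At 0.10 with full groups it is about 4 to 8 points. Contrasts between active arms are affected most, because both sides are grouped.

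The weight is moderate: the feasibility decision is not touched, but the between-arm intervals and the input to the definitive trial's sample size are.

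**What to change.** 1. Record a therapy-group identifier for every participant in the three active arms from the start of delivery, including those who attend few or no group sessions.
2. Replace ANOVA and chi-square for between-arm differences by a partially nested mixed model: a random therapy-group effect in the three active arms, TAU participants as singletons, and small-sample degrees of freedom. Use the logistic analogue for binary outcomes.
3. Report the therapy-group ICC with its confidence interval as a planned result for the definitive trial's sample size.

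The cost is one field on the session log and a change of wording in the analysis section. Trial status says that recruitment had not begun, so the field could be in place before the first group meets. The drawbacks are slightly wider intervals and, with about 8 groups per active arm, an imprecise ICC, which is why it should be given with its interval and not as a single figure.

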#### Process evaluation

One to one semi-structured interviews will be conducted with randomly selected participants from each intervention group to explore the engagement with intervention, acceptability of the sessions, perceived benefits and barriers. We are anticipating 10–12 interviews from each intervention group to reach category saturation. We will also interview up to 2 therapists of each intervention group to explore their experiences of delivering the study interventions including the factors that can impact intervention such as any environmental or cultural factors. The interview will be conducted either face-to-face or through telephone. Interviews will last between 50 and 60 min and will be digitally audio recorded on an encrypted voice recording device. For analysis of interviews, thematic analysis [30] with constant comparison approach of qualitative evaluation will be used and major subthemes emerging from data will be presented. All interviews will be transcribed and paraphrased in Urdu language to capture the qualitative richness of the participants understanding. To maintain the credibility and trustworthiness of the data and subsequent findings, the researchers will be supervised by senior and experienced qualitative researchers. Engagement in discussion and regular reviews by senior researcher will ensure fit of the data to the final analysis, and helped to minimise bias [49]. Analysis and writing will be guided by a quality checklist [50].

#### Health economics

A preliminary assessment of the costs to implement study interventions (MICBT, MBRP and CAMIAB) will be conducted. A change in scores of EQ-5D from baseline to 24th weeks will also be conducted to determine feasibility of an economic evaluation for a future definitive trial.

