#### Secondary outcomes

*The Maudsley Addiction Profile (MAP)* [42] is a brief questionnaire to measure problems in four domains that include substance use, health risk behaviour, physical and psychological health, and personal/social functions.

*The Short Warwick-Edinburgh Mental Well-being Scale (SWEMWBS)* [42] will be used to measure mental wellbeing. It consists of 7 statements on a 5-point Likert scale. The minimum scale score is 7 and the maximum is 35. The high score indicates better mental wellbeing.

*Quality of Life* [43] This will be measured using EuroQoL (EQ-5D) a standardised instrument to measure health outcomes and quality of life.

*Client Service Receipt Inventory (CSRI)* [44] will be used to estimate the health and social services received.

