### Data collection method

All participants (intervention and TAU groups) will undergo assessments at baseline, 3rd month (end of intervention) and at 6th month after randomisation. Participants will complete a self- report demographic information sheet (only at baseline) that will collect information related to age, duration of substance misuse, type of substance used etc., the MAP [47], SWEMWBS [42], EuroQoL (EQ-5D) [43] and CSRI [44]. All the assessments will be carried out by trained research assistants at baseline, 3rd month (end of intervention) and at 6th month.

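### The EQ-5D change from baseline to week 24 does not show whether an economic evaluation is feasible, and it leaves out the week-12 EQ-5D (minor)

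*Protocol article*

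**What the plan says.** The Health economics section of the protocol article has two elements. The first is a costing: "A preliminary assessment of the costs to implement study interventions (MICBT, MBRP and CAMIAB) will be conducted". The second is an EQ-5D analysis with a stated purpose: "A change in scores of EQ-5D from baseline to 24th weeks will also be conducted to determine feasibility of an economic evaluation". The purpose is directed at a later definitive trial. The section mentions neither the week-12 EQ-5D nor CSRI, and it does not mention treatment as usual (TAU).

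The data available are wider than that. Under Data collection method, participants in every arm "will undergo assessments at baseline, 3rd month (end of intervention) and at 6th month after randomisation", and EQ-5D and CSRI both belong to the battery given there: "All the assessments will be carried out by trained research assistants at baseline, 3rd month (end of intervention) and at 6th month". The abstract gives the same visits in weeks: "Assessments will be carried out at baseline, at 12th week (after completion of intervention) and 24th week post-randomisation". Under Secondary outcomes, CSRI "will be used to estimate the health and social services received".

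Two other sections bear on the point. Statistical analysis plans descriptive summaries of baseline and outcome data, with confidence intervals for group differences on every outcome measure. Primary outcomes lists completeness of assessment as a feasibility indicator, with a progression criterion above 70% at the end of the study.

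**The concern.** The protocol sets a method and a purpose side by side, and the method does not serve the purpose.

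- **Feasibility.** Whether a later economic evaluation can be carried out depends largely on whether participants complete EQ-5D and CSRI, at each visit and to a similar degree across arms. A mean change in EQ-5D carries no information on this. It could be large with half the forms missing, or zero with every form complete.
- **Quantity.** A cost-utility analysis would normally use QALYs over the follow-up period. A difference between two end points does not determine them, because it is silent on what happened between. The visit left out is the one at the end of the 12-week intervention.

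What is at stake is modest: the planners of the definitive trial would receive a figure that does not answer the question posed, although the data to answer it are already collected.

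**Working it through.** **Is there a figure to reproduce?** No. The article gives no utility, QALY, cost or expected EQ-5D effect. The utilities below are assumptions, chosen only to show how a change score relates to QALYs.

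**Inputs from the article.** EQ-5D at baseline (u0), week 12 (u12) and week 24 (u24); follow-up of 24 weeks = 24/52 = 0.4615 years.

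**Formula.** Area under the curve by the trapezoidal rule on three points:

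QALY = (12/52) × (u0 + u12)/2 + (12/52) × (u12 + u24)/2

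**Weights.** Collecting terms:

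- baseline: (12/52)/2 = 0.1154
- week 12: 12/52 = 0.2308
- week 24: (12/52)/2 = 0.1154

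The share of week 12 is 0.2308/0.4615 = 50%. The visit that the stated analysis omits carries as much weight as the other two together.

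**Change score fixed at 0** (assumed u0 = u24 = 0.60). Then QALY = 0.2308 × 0.60 + 0.2308 × u12:

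| u12 (assumed) | Change, baseline to week 24 | 24-week QALYs |
|---|---|---|
| 0.50 | 0 | 0.2538 |
| 0.60 | 0 | 0.2769 |
| 0.70 | 0 | 0.3000 |
| 0.80 | 0 | 0.3231 |

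**Change score fixed at 0.10** (assumed u0 = 0.60, u24 = 0.70). Then QALY = 0.1154 × (0.60 + 0.70) + 0.2308 × u12 = 0.1500 + 0.2308 × u12. This runs from 0.2654 at u12 = 0.50 to 0.3346 at u12 = 0.80.

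In both cases one and the same change score is compatible with a spread of 0.2308 × (0.80 − 0.50) = 0.069 QALYs. The spread depends only on the assumed range for week 12.

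**Can completeness be estimated usefully at this size?** Take 70% as an example, the level of the general completion criterion. The half-width of a 95% CI is 1.96 × √(0.7 × 0.3/n). With n = 65 per arm it is 0.111, and with all 260 it is 0.056. That is coarse by arm but informative overall, and it addresses feasibility directly.

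**The case against.** The case on the other side is substantial, and most of it stands as a limit on the point.

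- **Week 12 is not thrown away.** A reader of the Health economics section alone might infer that week-12 EQ-5D goes unused and that a benefit peaking then would be missed. The documents do not support that. EQ-5D is a listed secondary outcome, and the Statistical analysis section summarises outcome data with confidence intervals for each measure. The omission is confined to the health-economic analysis.
- **Feasibility does not rest on the change score alone.** It stands beside a costing, and the primary outcomes include a general completeness indicator with its threshold above 70%. This stands too. That criterion, however, is not broken down by instrument, refers to the end of the study, and is not linked to the economic evaluation.
- **Service use is collected in all arms.** One might infer from the Health economics section that resource use under TAU is ignored. It is not: CSRI is given to all participants, and the TAU section says existing services are monitored throughout. Only the costing of that information is unstated.
- **The protocol never proposes a two-point QALY.** It is tempting to set the area under the curve against a straight line from baseline to week 24 and quote a multiple as the error. That would measure an analysis that nobody planned, with utilities that nobody stated.
- **Referral after the intervention.** The article refers TAU participants onward after the intervention, and in the active arms those who need more or did not respond. One might take this as a reason to distrust week 24. It does not favour the change proposed here, since the area under the curve also uses week 24.
- **Absent QALY detail is not a fault.** A condensed article may leave it to the analysis plan, which is to be written before database lock. Agreed. The point rests on what is stated: a named analysis given a purpose that it cannot serve.

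**Conclusion.** The point holds in a narrow form. The Health economics section assigns the EQ-5D change from baseline to week 24 to a feasibility question that the size of a change cannot answer, and it leaves week 12 out of that analysis. The change score does not determine QALYs either: a change of 0 is compatible with 0.254 to 0.323 QALYs over 24 weeks. That range rests on assumed utilities (0.60 at baseline and week 24, 0.50 to 0.80 at week 12) and illustrates the principle; it does not estimate an error in this trial. The 50% weight of week 12 follows from the visit schedule alone.

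The severity is minor. The economic component is secondary and described as preliminary, and EQ-5D change enters no progression criterion, so no decision to proceed to a definitive trial would turn on it. The reason to act is that the improvement costs almost nothing.

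**What to change.** In the Health economics section, and in the analysis plan still to be written, replace the change score as the test of economic feasibility with:

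1. the percentage of participants with complete EQ-5D and with complete CSRI at each visit, by arm, as the economic feasibility measure;
2. exploratory 24-week QALYs by area under the curve from baseline, week 12 and week 24, with differences between arms adjusted for baseline EQ-5D and shown with 95% CIs;
3. a summary of CSRI service use and cost in all four arms, including TAU, beside the delivery costs of the three interventions.

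No new visits, instruments or participants are needed. The cost is a few lines of text and a little more analysis work, mainly in costing the CSRI data.
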